#### Sample size

A minimum sample size of 138 children (69 per group) is needed to test the equivalence between two interventions that do not differ by more than the minimum expected effect size of *d* = 0.50, which is slightly larger than the recommended minimum practical effect size indicated by Ferguson [47]. This calculation is based on the two one-sided tests (TOST) procedure for determining equivalence as outlined by Lakens [48] and using the authors´ TOSTER package for R, assuming equal group allocation, alpha = 0.05, 80% power, and four measurements. This sample size is also sufficient to detect within-subject changes in anxiety scores of the same magnitude (*d* = 0.50) over four measurements (WebPower; [49]). With this sample and allowing for a substantial violation of sphericity, the achieved power is 97%. Finally, an *N* = 138 with four measurements is sufficient for growth mixture modeling [50]. With an attrition rate of 15% [19, 51], we will have to recruit approximately 165 parents at T0 to achieve the final intended sample size.

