### Outcome measures

As depicted in Fig. 1, the parents and children will complete self-report questionnaires at baseline, mid-treatment (at 7 weeks for Emotion Detectives In–Out and 8 weeks for Coping Cat), posttreatment (at 15 weeks for Emotion Detectives In–Out and 16 weeks for Coping Cat), and follow-up (at 3 months). The (ADIS-IV-C) [44] will be administered at the screening phase, posttreatment, and follow-up.

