### Statistical methods

#### Efficacy evaluation

The efficacy of the Emotion Detectives In–Out in comparison with the Coping Cat will be assessed by analyzing the changes in the primary and secondary outcomes. As an equivalence clinical trial, the aim is to test whether the Emotion Detectives In–Out (experimental condition) is as effective as the Coping Cat (control group). The planned analysis for each outcome is a repeated-measures linear mixed model adjusted for covariates. The primary equivalence testing will be the between-group difference TOST at postintervention and at 3 months using the Welch correction for heterogeneous variance if needed. We will also investigate the linear and nonlinear (quadratic) effects for time and condition and simple effects for parameter estimates within each condition. For categorical variables (e.g., treatment response as assessed by CGI-I), treatment conditions will be compared using Pearson’s chi-square test.

To examine for heterogeneous intervention response, we will calculate Reliable Change Indices (RCI) for all participants at postintervention and at the 3-month follow-up. The RCI will be calculated for all outcomes and correlated with demographics to examine for subgroup efficacy predictors. The cutoff for clinically significant change is generally accepted as ± 1.96 [81]. Likewise, we aim to test the longitudinal trajectory of anxious symptoms over time using Growth Mixture Modeling (GMM). Furthermore, assuming that heterogeneous trajectories of anxious symptoms are observed, we aim to test the suitability of the collected demographic variables as predictors of group membership.

For the primary equivalence, efficacy, RCI, and chi-square analyses, we will use Jamovi software and the GAMLj and TOSTER packages as needed [82]. For GMM analyses, we will use R software with the package *lccm* [83] to perform growth mixture modeling, and evaluate various model specifications of *k* classes two through six, and using both fixed and random effects. We will select the optimal number of clusters was based on four criteria: parsimony, entropy approaching 1, lowest BIC/SABIC, and minimum class size > 10% of the sample [84, 85].

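### The unconditional statement that 138 children are enough for growth mixture modeling does not hold for moderately separated classes or for testing moderate class predictors, and the listed comparison cannot return a no-subgroups result

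*Protocol article*

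**What the plan says.** The Sample size section derives the number from the equivalence test: "A minimum sample size of 138 children (69 per group) is needed to test the equivalence between two interventions", with a "minimum expected effect size of *d* = 0.50" and "assuming equal group allocation, alpha = 0.05, 80% power, and four measurements". It next names the same effect size for within-subject change. It then adds, on one citation, that N = 138 "with four measurements is sufficient for growth mixture modeling". That last sentence states no class separation, class share, within-child correlation or predictor effect.

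The Efficacy evaluation section gives the growth mixture model two tasks. The first is to find trajectory classes. Models with two to six classes are compared, with fixed and with random effects, and the choice weighs parsimony, high entropy, the lowest BIC or SABIC, and a "minimum class size > 10% of the sample". The second applies if heterogeneous trajectories are seen: "we aim to test the suitability of the collected demographic variables as predictors of group membership".

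**The concern.** The sentence is an affirmative claim of adequacy in the sample-size section, not a detail left for later. Whether a mixture model works at a given N depends mainly on how far apart the classes are, how large the smallest is, and how strongly children's scores correlate over time. A statement without these conditions will be taken to cover whatever classes are reported and whatever predictors are or are not found.

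Two errors could follow. Classes may be reported that are spurious or so poorly separated that many children carry the wrong label. And the absence of a demographic predictor may be read as evidence that none matters, when the test had little chance of finding one.

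**Working it through.** **1. The plan's own figure.** TOST by normal approximation, margin 0.50, one-sided alpha 0.05, power 80%: n per arm = 2 × (z0.95 + z0.90)² / 0.50² = 68.5, so 69 per arm and 138 in total. This reproduces. Attrition: 138 / (1 − 0.15) = 162.4, consistent with the stated target of about 165. No figure is given for the mixture model, so there is none to reproduce.

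**2. Inputs.** From the article: N = 138, four occasions (baseline, 7 or 8 weeks, 15 or 16 weeks, 3-month follow-up), and the selection rule above. Assumed, because the article gives none: two true classes; difference in change of 0, 1, 1.5 or 2 SD; smaller class 30% or 50%; within-child correlation 0.5 or 0.7.

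**3. Finding classes.** Models with class-specific quadratic means were fitted by EM, with a random intercept (RI) or a random intercept and slope (RS). There were 120 runs per main cell, so Monte Carlo error is up to about 4–5 points. The 0 SD row has 30 runs, RI, with one to six classes offered.

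| Separation | BIC prefers two or more | SABIC prefers two or more |
|---|---|---|
| 0 SD | 0 of 30 | 10 of 30 (about 27% in a separate check) |
| 1 SD | RI 13–38%, RS 3–14% | 61–97% |
| 1.5 SD | RI about 95–100%, RS 23–85% | 100% (RI cell) |
| 2 SD | 97–100% | 100% (RI cells) |

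A separate set of runs with a smaller class of 20% or 35% and correlation 0.5 gave BIC detection of 62% or 88% at 1.5 SD, so that row depends on class share too.

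At 1 SD, mean entropy was 0.48–0.58 and 65–78% of children were correctly classified. At 2 SD (RI, correlation 0.5) the figures were 0.73–0.76 and 91–92%.

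The two criteria differ because of their penalties. A second quadratic class adds three means and one share, four parameters. BIC charges 4 × ln(138) = 19.7; SABIC charges 4 × ln((138 + 2)/24) = 7.1.

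**4. False classes.** With no random effects, a specification the plan includes, and no true classes, BIC chose two or more classes in 30 of 30 runs, three classes in 27 of them.

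**5. Predictors with perfect classification.** This step needs no mixture model. The assumed predictor is binary, with odds ratio 2 and prevalence 30% or 50% in the reference class. The other class then has p1 = 2 × odds / (1 + 2 × odds): 0.30 becomes 0.46 and 0.50 becomes 0.67. Power of a two-sided 5% two-proportion test, computed from the binomial distributions with n1 + n0 = 138:

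| Class of interest | Power |
|---|---|
| 14 (just over 10% of 138 = 13.8) | 22–25% |
| 28 | 35–37% |
| 41 | 44–46% |
| 69 (even split) | about 50% |

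**6. Predictors with fitted classes.** At 1 SD, for a predictor differing by d = 0.5 between classes, power on modal class was 8–38%, against 73–88% if true class were known. At d = 0.3 it was 3–14%, and at d = 0.8 it was 30–45%. At 2 SD and d = 0.5 (RI, correlation 0.5) it rose to 57–71%.

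**The case against.** The strongest reply is that every magnitude rests on inputs that the article does not give. This stands. Nothing in the article makes 1 SD the relevant separation, and the margin of 0.50 does not help, because it is a between-arm mean difference and not a gap between latent classes. At 2 SD the size does find two classes, so the sentence is true over part of the range. The cited source is not at hand, so the conditions it sets are unknown. None of this rescues an unconditional statement.

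A reader might infer that moderately different classes would usually be missed. That is true of BIC but not of SABIC, which the plan also names. SABIC's higher detection comes with false classes in about a quarter to a third of runs. A null result is also not the likeliest failure: no one-class model is among those listed, although the conditional wording of the predictor step presumes that heterogeneity might not be seen.

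A reader might also infer one fixed low power for class predictors, or failure at every separation. The figures do not support that: power at 1 SD runs from 3% to 45% according to the predictor effect, and is higher at 2 SD.

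It can also be said that the sentence claims nothing about predictors. That is literally so, but predictor testing is one of the two uses planned for the classes. Finally, the plan already correlates reliable change indices with demographics, so a route that avoids classes exists in part.

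**Conclusion.** The concern holds in limited form. The unqualified sufficiency statement is not supported for classes about 1 SD apart, nor for class predictors of moderate effect. On the assumed inputs, two classes are recovered reliably only at about 2 SD; at 1.5 SD the result depends on the random-effects model and class share. For odds ratio 2, power is at most about 50% even with perfect classification and an even split, and about 22–25% at the smallest class the plan accepts. With no one-class model listed, the main risk is spurious or poorly separated classes.

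It does not follow that the trial is too small, or that growth mixture modeling at 138 is uninformative in general. This is a heterogeneity analysis; the equivalence sample size reproduces and is untouched.

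**What to change.** In Sample size, replace the sentence with one saying that 138 children with four measurements are adequate only for widely separated trajectory classes. State the assumed separation and class shares, and add that the size is not powered for class predictors of moderate effect.

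In Efficacy evaluation:
- add a one-class model to the comparison;
- label the mixture model and its predictors exploratory, and say that absence of predictors is inconclusive;
- examine demographic predictors of change in the planned mixed model as well, which avoids class misassignment.

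The cost is a few sentences, one further model fit and a less favourable claim. No more children are needed.

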#### Randomization

##### Sequence generation

After the children and parents fill out the baseline (T0) assessment measures, they will be randomly assigned at each recruitment location by a researcher not collaborating in the study and through an automated, web-based randomization program to one of two conditions: the experimental condition (Emotion Detectives In–Out) and the active control condition (Coping Cat). A permuted block randomization procedure will be employed in each location to obtain groups with an equivalent number of participants. The block size will depend on the number of eligible children in each location, but it is expected to be between 10 and 12 so that 5 to 6 participants can be assigned to each condition.

##### Concealment mechanism

The allocation sequence will be generated in a web-based randomization program by a researcher who is not collaborating in the study and who has no role in determining the eligibility and entry of participants in the study. The allocation sequence will then be provided to the researchers, who will communicate the randomization result to the parents via telephone.

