## Methods

### Trial design

This study is designed as an equivalence randomized controlled parallel-group two-arm trial (allocation ratio 1:1) to compare a new blended group intervention (Emotional Detectives In–Out) with a face-to-face group intervention (Coping Cat) for children with anxiety disorders. The Coping Cat intervention was chosen as the active control group because it is an evidence-based cognitive-behavioral intervention for children with anxiety disorders [40, 42] that can be used to test the equivalence of the Emotion Detectives In–Out intervention in reducing anxiety symptomatology. An equivalence trial aims to demonstrate that a novel or non-established treatment is as effective as a well-established treatment within a prespecified margin of equivalence. In the current trial, the margin of equivalence was defined as the difference between the intervention groups that would be considered the minimum clinically relevant difference.

The clinical trial is registered at ClinicalTrials.gov (identifier: NCT05747131, date assigned February 28, 2023). Authorization for sample recruitment was obtained from the Ethics Committee of the Faculty of Psychology and Education Sciences of the University of Coimbra and from the Ethics Committee of the Faculty of Psychology of the University of Lisbon. The clinical trial will follow the ethical recommendations of the American Psychological Association (APA, 2010) and the World Medical Association’s Declaration of Helsinki (World Medical Association, 2013).

The SPIRIT (Standard Protocol Items: Recommendations for Intervention Trials) checklist of information [43] and the CONSORT recommendations for noninferiority and equivalence trials [41] will be used as guidance to report the study protocol of this clinical trial.

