##### Blinding

This clinical trial will be an open-label trial because both the researchers and the participants will know which treatment they receive. However, the participants will not know which intervention is the experimental condition and which is the control condition to avoid expectations about the efficacy of the new intervention and the comparison intervention.

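### The concealment step gives the allocation sequence itself to the open-label team, and the article does not say that a block is closed before this happens

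*Protocol article*

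**What the plan says.** All of the relevant text is in the protocol article, under Randomization.

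- **Sequence generation** places randomization after baseline: "After the children and parents fill out the baseline (T0) assessment measures, they will be randomly assigned at each recruitment location". The assignment is made "by a researcher not collaborating in the study and through an automated, web-based randomization program". The method is stated as "A permuted block randomization procedure will be employed in each location to obtain groups with an equivalent number of participants", and on size: "The block size will depend on the number of eligible children in each location, but it is expected to be between 10 and 12". Trial design gives the ratio as 1:1.
- **Concealment mechanism** says that the outside person generates the sequence and describes that person as someone "who has no role in determining the eligibility and entry of participants in the study". The next sentence is the handover: "The allocation sequence will then be provided to the researchers, who will communicate the randomization result to the parents via telephone".
- **Blinding** adds: "This clinical trial will be an open-label trial because both the researchers and the participants will know which treatment they receive".

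Two other sections show what the trial team does before randomization. Under Participant recruitment, the research team contacts parents of children referred by schools and confirms the main eligibility criteria. Under Participant selection, eligibility is settled in an interview led by a clinical psychologist, and consent and the baseline measures follow.

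**The concern.** Independent generation and concealment are separate protections. Generation by an outsider keeps the order of allocations free of influence. Concealment keeps the people who decide on entry from knowing the next allocation. The article secures the first. It then describes a step that, read literally, gives up the second, because the remaining sequence is in the hands of the study team.

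This matters because entry involves judgement. A child may be admitted on clinically significant symptoms without a full diagnosis, and Participant selection classes a child as subclinical partly on whether symptoms affect daily life. Someone who knows the next allocation could, without intending to, be readier to admit or defer a particular child. Case mix could then differ between arms. In an equivalence trial such a difference can work either way: it may produce an apparent difference or hide a real one.

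**Working it through.** The article gives no figure for concealment, so the check is mainly a comparison of passages. The planned total of 138 (69 per group) does not depend on this point and stays as it is.

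**Step 1: who assigns?** Under Sequence generation, the outside researcher assigns children through the web program. If so, the team needs only each child's result. Under Concealment mechanism, the team receives the sequence. The two subsections do not describe the same flow of information.

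**Step 2: who receives it?** The text says only that it goes to the researchers. Blinding states that the researchers know the treatments. Participant recruitment gives the research team a part in confirming eligibility for school referrals. Overlap between those who hold the sequence and those who influence entry is therefore plausible, but it is not stated.

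**Step 3: when is it released?** Sequence generation puts a child's randomization after that child's baseline. It does not say that all children in the block have reached that stage before the sequence is released. Two cases follow:

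| Order of events | Allocations known to the team when eligibility is decided |
|---|---|
| Whole block has eligibility, consent and baseline complete, then release | None (0%) |
| Release, then a further child is considered for the same block | All remaining ones (100%) |

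The article does not say which case applies.

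**Step 4: do the other safeguards cover the second case?**
- The generator's lack of any role in entry protects the making of the sequence, not its use after handover.
- Intention-to-treat analysis of all who completed baseline (Attrition, nonadherence and missing data) keeps withdrawn families in the analysis. It does not correct who was let in.
- Covariate adjustment (Covariates) names age, sex, comorbidity, medication and previous treatment. It cannot correct selection on unmeasured features.

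**Step 5: how often would the handover occur?** About 165 are to be recruited. With blocks of the expected size, 165/12 = 13.75 and 165/10 = 16.5, so roughly 14 to 17 blocks, each with its own release. This assumes blocks of 10 to 12 throughout.

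**The case against.** The strongest reply is that the article can be read as batch randomization. Block size depends on the number of eligible children at a location, both arms are weekly group programmes that suit batch formation, and baseline comes before assignment. On that reading the children are already counted and enrolled when the block is drawn, so there is no entry left to steer. The handover sentence ends with telephoning results to parents, so sequence may be loose wording for a batch's results. A condensed article may also leave locking and release details to the full protocol. The batch reading is natural, and if it is what is meant the risk at entry is zero. But it rests on a condition that neither subsection states. Nor is this simply a missing detail: the handover is a stated procedure under the heading meant to establish concealment.

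A reader might go further and infer any of the following, none of which the document supports:

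- **That block size equals the number of eligible children and is known to the team.** The text says that size depends on that number and gives an expected range.
- **That late or replacement children are placed in vacated slots.** Data monitoring and Ethics and dissemination describe ways in which a child may leave or be redirected, but no replacement is provided for.
- **That allocations can be guessed about 65% of the time.** For a 1:1 block of 2m, guessing the arm with more slots left gives m + (4^m/C(2m,m) − 1)/2 expected correct guesses. For m = 5 this is 5 + (1024/252 − 1)/2 = 6.53 of 10, or 65.3%. For m = 6 it is 6 + (4096/924 − 1)/2 = 7.72 of 12, or 64.3%. The arithmetic is right, but it assumes that children enter one at a time into a partly filled block of known size with earlier allocations visible. The article describes no such procedure, so these figures do not measure its risk.

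**Conclusion.** The point holds in a limited form. As worded, the plan gives the sequence to the unblinded team and does not make release conditional on the block being fully enrolled. Concealment is not secured for any child whose eligibility is decided after release. The size is conditional: none if every block is closed first, complete foreknowledge of the remaining allocations if it is not. The document does not show that any child enters after release, so it does not support saying that entries will be steered. It supports saying only that the text does not prevent it. The conclusion rests on taking the word sequence literally and on some overlap between those who hold it and those who influence entry. It should be corrected, because the remedy is nearly free, but it does not affect the sample size or the planned analysis.

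**What to change.** Reconcile Sequence generation and Concealment mechanism, replacing the handover sentence with a procedure along these lines:

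1. The outside researcher and the web program keep the sequence; the trial team never receives it.
2. For each batch at a location, the team submits a list of identifiers for children with confirmed eligibility, consent and completed baseline.
3. The program returns one allocation per listed identifier, and the team telephones these results to parents.
4. Any child who enters later is randomized centrally in a new batch and is not placed in a slot vacated after allocation.

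If this is already the practice, stating it is enough. The outside researcher and the web program are already planned, so the cost is protocol wording. The downside is practical: a late child may wait for the next batch, or a group may run one child short.

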##### Blinding

This clinical trial will be an open-label trial because both the researchers and the participants will know which treatment they receive. However, the participants will not know which intervention is the experimental condition and which is the control condition to avoid expectations about the efficacy of the new intervention and the comparison intervention.

